#### *Mediators of physical activity change*

The Physical Activity Maintenance Assessment (PAMA) will be used to measure participant motivation (10 items), self-efficacy (5 items) and confidence in maintaining physical activity (3 items). Responses will be measured on a 5-point Likert Scale ranging from ‘very unlike me’ to ‘very much like me’. Evidence shows that the PAMA has predictive validity with other accepted measures of physical activity (e.g. VO_2_ max and energy expenditure, as measured by the 7-Day Physical Activity Recall) and other health characteristics that are associated with regular physical activity (e.g., lower body mass index and reduced scores on the Beck Depression Inventory [47].

#### *Functional status and quality of life*

Functional status and quality of life will be measured using the Australian adaptation of the Short Form (36) Health Survey (SF-36) [48]. The SF-36 comprises 36 items representing eight domains of health and quality of life: vitality; physical functioning; bodily pain; general health perceptions; physical role functioning, emotional role functioning; social role functioning; and mental health. By combining these eight domains, two further subscales are derived: Physical Component Scale (PCS) and Mental Component Scale (MCS). Where necessary, scales are reverse-scored so that a higher score indicates better health. The SF-36 has been used in other studies of lifestyle interventions among cancer survivors and in self-management interventions in chronic disease [49,50]. Consistent with reliability analysis of the American version, all scales of the Australian version of the SF-36 demonstrate high internal consistency, with Cronbach’s alpha ranging from 0.81 (General Health) to 0.92 (Physical Functioning and Bodily Pain). The median of item-scale correlations within each scale ranged from 0.61 (Mental Health) to 0.82 (Role-Physical) [47].

#### *Demographics*

A brief questionnaire will be used to assess demographic characteristics including age, gender, marital status, ethnicity, level of education, cancer type, cancer stage at diagnosis and treatment type(s).

### Statistical considerations

#### *Sample size calculation*

A priori power calculations determined that a sample of 44 participants per group (n = 88) is needed to detect moderate effect sizes (r = 0.30-0.50) with 80% power and a significance level (alpha) of 0.05. Allowing for 20% dropout, 55 participants are required per group. Allowing for adjustment by baseline measure (r = 0.05) a total of 41 participants per group (n = 82) will be recruited.

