## Methods/Design

### Participants and setting

The STRIDE study is a quasi-randomised controlled intervention trial. Participants will be allocated to either the intervention group or the wait-list control group. Approximately 80 participants will be recruited and randomised by the research investigator(s). Table 1 shows the inclusion and exclusion criteria.

**Table 1 T1:** Inclusion and exclusion criteria

**Inclusion criteria**	**Exclusion criteria**
• Age over 18 years, no age limit higher	• Patient with metastasis,
• Have had cancer treated with curative intent (excluding skin cancer)	• Pregnant or intending to become pregnant during study period,
• Not undergoing active treatment (including chemotherapy and radiotherapy but will be included if taking long-term follow-up medications or therapies such as hormone therapy)	• Physical or psychological condition (i.e. cognitive decline) that may impede their participant in the study
• Permanent resident of South Australia,	
• Insufficiently active (engaging in less than 20 sessions of physical activity, one session lasting 30 minutes) over the past month determined by The Active Australia Survey [22]	
• Regular access to the internet (whether it be personal access or through a library or community centre)	
• Sufficient English language skills and cognitive ability to complete questionnaires,	
• Satisfy stage one of the pre-exercise screening guidelines for commencing exercise determined by the Sports Medicine Australia Pre-Exercise Screening System [23]	
• Approval by treating doctor to be part of the study,	
• Provide written informed consent	

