### Randomisation and blinding

Participants will be randomly allocated to one of the two trial arms (intervention or wait-list control). A block design with allocation weight of 3:3 will be used to generate treatment allocation. It is not possible for three key researchers (LF, DZ, RS) to be blinded to participants’ group allocation as they will be performing the information sessions relevant to each group. It is not possible to blind participants to group allocation due to the nature of the intervention. Six other research assistants performing physical and questionnaire measurements will be blinded to the participants’ group allocation.

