#### *Analytic plan*

Data will be entered and analysed using the IBM SPSS version 21 (SPSS, Inc, Chacago, IL) statistical software package. The intent-to-treat principle will be applied and the significance level will be set at 0.05. Baseline comparisons of demographic outcomes will be performed using independent samples t-tests. The primary outcome (number of steps/day) will be reported as independent samples t-tests comparing change scores in the two randomisation groups. Change scores for the secondary outcomes (health measures, diet quality and quality of life) will be calculated for each variable and compared between treatment and control groups using parametric or non-parametric procedures as appropriate for the data distributions.

Random effects mixed modelling will be used with time (0, 12, and 24 weeks) and group allocation (Intervention, Control) as the fixed factors. A time by group interaction term will be used to formally test the aims of the study.

Time by region (rural versus metropolitan) repeated measures ANOVA will be used to examine differences in the primary and secondary outcomes between groups over time. Sociodemographic factors and diet will be controlled for in the analysis.

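### The printed baseline correlation (r = 0.05) does not turn 55 per group into 41; only about 0.50 does, and 80% power then needs a baseline-adjusted primary analysis that the plan does not name

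*Protocol article*

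**What the plan says.** The protocol article, under Sample size calculation, builds the recruitment target in three steps.

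1. It starts from "a sample of 44 participants per group (n = 88" in total), which "is needed to detect moderate effect sizes (r = 0.30-0.50") "with 80% power and a significance level (alpha) of 0.05". The sidedness of the test, the SD of steps per day and the difference in steps are not given.
2. It adds an allowance for loss: "Allowing for 20% dropout, 55 participants are required per group".
3. It then reduces the number: "Allowing for adjustment by baseline measure (r = 0.05) a total of 41 participants per group (n = 82) will be recruited".

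Under Analytic plan, the primary test is named: "The primary outcome (number of steps/day) will be reported as independent samples t-tests comparing change scores in the two randomisation groups". The same section adds a mixed model with a time by group interaction. Neither is described as having baseline steps as a covariate. Allocation is equal ("A block design with allocation weight of 3:3 will be used to generate treatment allocation").

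**The concern.** The third step removes 14 participants per group, a quarter of the requirement (from 110 to 82 in total), and rests on one input. A correlation of 0.05 between baseline and follow-up is close to none, and adjusting for a covariate with almost no predictive value saves almost no participants. The printed input and the printed sample size therefore do not belong together.

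The analysis matters as well. The (1 − r²) saving belongs to a model in which baseline steps are a covariate. A t-test on change scores has a different variance and does not inherit that saving. If the reduction was taken for one analysis and the primary test is another, the 80% figure does not describe the test that will be reported, and a null result could be read as stronger evidence of no effect than it is.

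**Working it through.** The article uses r for two things. Below, r is the effect size and ρ is the correlation of baseline with follow-up steps. Equal variances at the two times and a two-sided 5% test are assumed.

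**Inputs from Sample size calculation.** 44 per group before allowances; 80% power; alpha 0.05; 20% dropout; ρ = 0.05; 41 per group recruited.

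**Dropout step.** 44 / (1 − 0.20) = 55. This reproduces.

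**Baseline step with ρ = 0.05.** n × (1 − ρ²) = 55 × (1 − 0.0025) = 54.9, so 55 per group. Other readings:

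- Factor applied before dropout: 44 × 0.9975 = 43.9, rounded to 44; 44 / 0.8 = 55.
- 0.05 read as ρ²: 55 × 0.95 = 52.25, or 53 if applied before dropout.
- Change-score factor 2(1 − ρ): 55 × 1.90 = 104.5.

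None gives 41.

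**Correlation that does give 41.** ρ = √(1 − 41/55) = 0.505, or 0.495 to 0.513 allowing for rounding of 41. With ρ = 0.50: 55 × 0.75 = 41.25.

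**Effect size for the power check.** The protocol gives only a range, so the effect is back-solved: a two-sample t-test with 44 per group has 80% power at d = 0.604. This is an assumption, and it lies close to the lower end of the protocol's range, since r = 0.30 converts to d = 2r/√(1 − r²) = 0.63.

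**Number analysed.** 41 × 0.8 = 32.8, about 33 per group.

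**Power at 33 per group**, with d scaled to the SD of a single measurement. The variance factor is 1 − ρ² for ANCOVA and 2(1 − ρ) for the change score; the effective d is 0.604 / √factor.

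| ρ | Analysis | Factor | Effective d | Power |
|---|---|---|---|---|
| 0.50 | ANCOVA | 0.75 | 0.698 | 80% |
| 0.05 | ANCOVA | 0.9975 | 0.605 | 68% |
| 0.50 | change-score t-test | 1.00 | 0.604 | 68% |
| 0.05 | change-score t-test | 1.90 | 0.438 | 42% |

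The protocol does not say which SD the effect is scaled to. At ρ = 0.50 this makes no difference to the change-score row, because the SD of change then equals the SD of one measurement (factor 1). At ρ = 0.05 it does: 42% would be about 68% if the effect were scaled to the SD of change.

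**Over the protocol's effect range.** Unadjusted comparison, 33 per group:

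| r | d | Power |
|---|---|---|
| 0.30 | 0.63 | 71% |
| 0.33 | 0.70 | 80% |
| 0.50 | 1.15 | over 99% |

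On this unadjusted basis, which is also the change-score t-test at ρ = 0.50, the shortfall lies at the lower end of the range.

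**The case against.** The strongest reply is that 0.05 is a slip for 0.50. The match at 41.25 is close, and under that reading 33 analysed per group do have 80% power in a baseline-adjusted analysis. That stands. A reader might infer from the arithmetic that the trial is underpowered, or 14 per group short of its own requirement. The document does not support that as a flat statement: it holds only if 0.05 was really meant or if the analysis does not adjust for baseline.

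A second reply is that d of about 0.60 is not the protocol's figure, and that effects a little above the lower end of its range are detectable with 33 per group even without adjustment. That also stands, and it limits the size of the problem. It does not restore the stated derivation, because 44 per group implies an effect near that lower end.

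A third is that the mixed model might supply the baseline adjustment. As described, it has time and group as fixed factors and an interaction. With complete data its group difference in change from baseline to week 12 is the same contrast as the change-score comparison. The article names no constraint or covariate that would add the ANCOVA gain.

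A reader might also set 82 against the figure under Participants and setting: "Approximately 80 participants will be recruited and randomised by the research investigator(s"). These do not conflict; 82 is approximately 80.

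**Conclusion.** The printed correlation is wrong for the printed sample size: ρ = 0.05 leaves 55 per group, and 41 requires about 0.50. This part rests on arithmetic alone. A misprint is the likely explanation, but the document cannot confirm it.

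The 80% power is conditional. Of the four combinations of correlation and analysis, only ρ = 0.50 with ANCOVA delivers it, and that combination matches neither the printed correlation nor the named primary test. Correcting the digit alone therefore does not support 41 per group: with the change-score t-test at ρ = 0.50, power is about 68%. These figures assume d of about 0.60 (back-solved), a two-sided 5% test, equal variances at the two times and 20% dropout; the 42% figure further needs the effect to be scaled to the single-measurement SD.

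**What to change.** State in Sample size calculation the correlation actually used, and which SD the effect size refers to.

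- **If it was 0.50:** correct the printed value, say that 41 per group holds for a baseline-adjusted analysis, and change the primary analysis in Analytic plan to an ANCOVA of steps per day adjusted for baseline steps.
- **If 0.05 is meant, or the change-score t-test stays primary:** keep 41 per group, but restate the power or the detectable effect under that analysis. With the t-test at ρ = 0.50, for example, that is about 68% power at d of about 0.60, or 80% power at d of about 0.70.

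The cost is a corrected number, a revised sentence or two and, in the first case, a change of primary model. Baseline steps are already collected, so no new data and no extra participants are needed. In the second case the stated power becomes less favourable.

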#### *Analytic plan*

Data will be entered and analysed using the IBM SPSS version 21 (SPSS, Inc, Chacago, IL) statistical software package. The intent-to-treat principle will be applied and the significance level will be set at 0.05. Baseline comparisons of demographic outcomes will be performed using independent samples t-tests. The primary outcome (number of steps/day) will be reported as independent samples t-tests comparing change scores in the two randomisation groups. Change scores for the secondary outcomes (health measures, diet quality and quality of life) will be calculated for each variable and compared between treatment and control groups using parametric or non-parametric procedures as appropriate for the data distributions.

Random effects mixed modelling will be used with time (0, 12, and 24 weeks) and group allocation (Intervention, Control) as the fixed factors. A time by group interaction term will be used to formally test the aims of the study.

Time by region (rural versus metropolitan) repeated measures ANOVA will be used to examine differences in the primary and secondary outcomes between groups over time. Sociodemographic factors and diet will be controlled for in the analysis.

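### Recruitment was cut from 55 to 41 per group for baseline adjustment, but the change-score t-test named for steps/day does not earn that cut

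*Protocol article*

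**What the plan says.** All of this is in the protocol article, under Statistical considerations.

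**Sample size calculation.** The starting point is that "a sample of 44 participants per group (n = 88) is needed", "with 80% power and a significance level (alpha) of 0.05", for an effect given on a correlation scale as r = 0.30 to 0.50. No SD and no difference in steps/day are given. Then: "Allowing for 20% dropout, 55 participants are required per group". Then: "Allowing for adjustment by baseline measure (r = 0.05) a total of 41 participants per group (n = 82) will be recruited".

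**Analytic plan.** "The primary outcome (number of steps/day) will be reported as independent samples t-tests comparing change scores in the two randomisation groups". For the rest, "Change scores for the secondary outcomes (health measures, diet quality and quality of life) will be calculated for each variable" and compared between groups by a parametric or non-parametric method.

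The next paragraph adds a mixed model with time (0, 12 and 24 weeks) and group as fixed factors, and says that its time by group interaction will formally test the study aims. Baseline steps/day is not named as a covariate in any analysis. The only covariates named are sociodemographic factors and diet, in the paragraph on region.

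**The concern.** The final recruitment target takes credit for a gain in precision from baseline adjustment. That credit belongs to an analysis with the baseline value as a covariate. Subtracting baseline is a different operation with a different variance, and at the correlation that reproduces the 41 it gains nothing over analysing follow-up values alone.

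The stated 80% power supports recruiting 82 people. If the test actually used does not deliver the assumed precision, the trial is smaller than its own calculation requires, and a null result on steps/day would be hard to interpret. The plan also leaves unclear whether the t-test or the interaction decides the primary question, so a reader cannot tell which test the 80% refers to.

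**Working it through.** Two quantities are called r in the plan. Here r is the effect size (0.30 to 0.50) and ρ is the correlation between baseline and follow-up steps/day.

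**Inputs from the protocol article:** alpha 0.05; power 80%; 44 per group before adjustments; 20% dropout; 41 per group recruited; printed ρ = 0.05; equal allocation (3:3).

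**Assumptions not in the document:** a two-sided test; equal SDs at baseline and follow-up; an effect standardised on the follow-up SD.

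**1. Reproduce the plan's figures.**
- Dropout: 44 / 0.80 = 55. Reproduces.
- ANCOVA factor 1 − ρ² at the printed ρ = 0.05: 55 × 0.9975 = 54.9, so 55. Does not give 41.
- ANCOVA factor at ρ = 0.50: 55 × 0.75 = 41.25, so 41. Reproduces.

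The cut is therefore an ANCOVA reduction at ρ = 0.50. The printed 0.05 is probably a misprint, which is a separate error.

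**2. Apply the factor of the stated test.** The variance of a change score, relative to the follow-up variance, is 2(1 − ρ).
- At ρ = 0.50: 2 × 0.50 = 1.0, so 44 analysed and 55 recruited per group are still needed.
- The factor reaches 41/55 only at ρ = 1 − (41/55)/2 = 0.63, a value that the plan does not state.

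**3. Effect size assumed.** The standardised difference that 44 per group detects with 80% power is d = (1.96 + 0.84)/√(44/2) = 0.597 (0.604 by the noncentral t).

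**4. Power with the planned recruitment.** Analysed per group: 41 × 0.80 = 32.8, about 33. Power ≈ Φ(d√(n/2)/k − 1.96), where k² is the variance factor. With d√(33/2) = 2.426 and ρ = 0.50:
- Change score, k = 1: Φ(2.426 − 1.96) = 68% (67% by the noncentral t).
- ANCOVA, k = √0.75 = 0.866: Φ(2.802 − 1.96) = 80%.
- Change score with no dropout, 41 analysed: 77%.

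**5. Sensitivity to ρ, 33 analysed per group.**

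| ρ | Change score | ANCOVA |
|---|---|---|
| 0.30 | 54% | 72% |
| 0.40 | 60% | 75% |
| 0.50 | 68% | 80% |
| 0.60 | 77% | 86% |
| 0.63 | 81% | 88% |
| 0.70 | 88% | 92% |

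The ratio of change-score to ANCOVA variance is 2/(1 + ρ), which is never below 1. At the printed ρ = 0.05 the figures would be 42% and 68%, but that value cannot produce the plan's 41, so they are conditional only.

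**6. Sensitivity to the effect.** Converting by d = 2r/√(1 − r²) for equal groups, with ρ = 0.50, 33 analysed and the noncentral t:
- r = 0.30 (d = 0.63): change score 71%.
- r = 0.33 (d = 0.70): 80%.
- r = 0.50 (d = 1.15): over 99%.

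**7. The mixed model.** Week 0 is a level of time, so baseline is a response. With an unconstrained group effect and complete data, the week-12 time by group contrast equals the difference in mean change. It has the change-score variance, not the ANCOVA variance.

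**The case against.** A change-score t-test is valid and unbiased under randomisation, and it does use baseline. That stands: the issue is precision, not bias, and the test is unadjusted only in the sense of having no baseline covariate.

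A reader might infer that the planned test cannot reach 80% power at all. The documents do not support that. The d of about 0.60 is back-solved from 44 per group. The plan states a range of effects, and above roughly r = 0.33 the change-score test reaches 80% with 33 per group even at ρ = 0.50. It also does so at the assumed d once ρ is about 0.63 or more. What remains is that a power claim should hold at the smallest effect of the stated range, where the test falls short at the ρ that reproduces 41.

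A reader might also take the 42% at the printed correlation as the true power. That value is inconsistent with the plan's own arithmetic, and ANCOVA would not reach 80% there either. Moreover, if the effect were standardised on the change-score SD, power with 33 per group would be about 68% whatever ρ is.

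Nor is the t-test clearly the sole primary test, since the interaction is given the role of testing the aims. This does not rescue the calculation: as written, that contrast gains nothing over the change score at week 12.

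Finally, a journal article may leave detail to a fuller plan. Here, though, both the basis of the sample size and the test are stated, and they do not match.

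**Conclusion.** The point holds in limited form. The saving from 55 to 41 per group belongs to ANCOVA at ρ = 0.50, and neither of the stated group comparisons of steps/day earns it. At that correlation the cost is about 12 percentage points of power: 68% instead of 80%. This rests on d of about 0.60 (inferred), equal SDs at the two times, a two-sided test and about 33 analysed per group. It is a shortfall at the low end of the stated effect range and at correlations below about 0.63, not across the board. The secondary outcomes use the same approach, but no stated power depends on them.

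**What to change.** - In the Analytic plan, name one primary test for steps/day. Make it ANCOVA of follow-up steps/day on group with baseline steps/day as covariate, or the planned mixed model with baseline as covariate or with baseline means constrained equal between arms. Report the adjusted mean difference with its 95% CI.
- In the Sample size calculation, correct the printed correlation so that it yields the stated 41, and say which analysis the reduction assumes.
- If change scores are kept, restate the power (about 68% at ρ = 0.50 with 41 recruited per group, under the assumptions above) or return to 55 per group.
- The same baseline-adjusted model can serve the continuous secondary outcomes. This is optional.

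The first two changes cost a few lines of wording. Baseline steps/day is already measured in all participants, so there is no added burden, and ANCOVA is at least as precise as the change score at every correlation. Only the return to 55 per group would need more recruitment, 14 more per group.

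### Two different analyses are attached to the primary outcome, with no statement of which one decides or at what time point, and neither is the baseline-adjusted comparison on which the sample size was reduced

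*Protocol article*

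**What the plan says.** The Analytic plan section states: "The primary outcome (number of steps/day) will be reported as independent samples t-tests comparing change scores in the two randomisation groups". The interval over which change is taken is not given, and the tests are in the plural. The Outcome measures section lists three assessments (baseline, end-program at week 13, and 3-month follow-up), so two changes from baseline are possible.

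The next paragraph of the same section brings in a second analysis: "Random effects mixed modelling will be used with time (0, 12, and 24 weeks) and group allocation (Intervention, Control) as the fixed factors". It continues: "A time by group interaction term will be used to formally test the aims of the study". The main aim is to increase walking, so this test also bears on steps/day.

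The error rate is set once: "The intent-to-treat principle will be applied and the significance level will be set at 0.05".

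The Sample size calculation section starts from "a sample of 44 participants per group (n = 88"), raises this to 55 per group for 20% dropout, then lowers it to 41 per group on the grounds of adjustment for the baseline measure, with a printed correlation of 0.05. It names no test and no time point.

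**The concern.** The two analyses ask different questions. A change-score t-test compares the groups over one interval. With time as a three-level factor, the time-by-group interaction is an omnibus test on 2 degrees of freedom. It can be significant because of a difference at 12 weeks, at 24 weeks or both, in either direction, and does not by itself say which.

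If the two disagree, the article gives no basis for settling the matter without looking at the data. The headline claim would then depend on which result is put forward, and the 5% level would no longer describe the chance of a false positive claim. The reduction to 41 per group also relies on an efficiency gain that a change-score t-test does not deliver.

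**Working it through.** **Inputs from the article.** Level: "the significance level will be set at 0.05" (two-sided assumed). Design: "80% power and a significance level (alpha) of 0.05". Effect: "needed to detect moderate effect sizes (r = 0.30-0.50"), with no SD and no difference in steps. Dropout 20%. Final size 41 per group.

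**Assumed inputs.** Equal correlation between any two visits (0.5 unless stated), complete data in the simulations, and a 0.6 SD effect where power is shown.

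**1. The plan's own figure.** A correlation test at r = 0.30 needs ((1.960 + 0.842)/atanh(0.30))² + 3 = 84.9 in total, or 43 per group. A two-mean comparison with d = 0.60 needs 2 × (1.960 + 0.842)²/0.60² = 43.6, or 44 per group. The printed 44 is therefore reproduced closely, although d = 0.60 is not stated. Dropout: 44/0.80 = 55. Baseline adjustment: 55 × (1 − 0.50²) = 41.25, whereas the printed 0.05 gives 55 × (1 − 0.05²) = 54.9. The final 41 thus follows from a baseline-adjusted comparison with correlation 0.50.

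**2. Type I error.** Simulated null trials: 41 per arm, correlation 0.5, 40,000 trials, random-intercept F test for the interaction.

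| Rule for claiming success | Type I error |
|---|---|
| One prespecified test | about 0.05 |
| Week-12 t-test or interaction | about 0.075 |
| Week-12 or week-24 t-test | 0.091 |
| Either t-test or interaction | about 0.10 |

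Results are almost the same at correlations 0.05 and 0.7 (0.077 and 0.075 for the second row). If the tests were independent, the figures would be 1 − 0.95² = 0.0975 for two and 1 − 0.95³ = 0.143 for three.

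**3. Power of the 2-df interaction against a 1-df week-12 test.** Take non-centrality 7.85, which gives 0.80 on 1 df. With equal correlation between visits, the two changes from baseline correlate 0.5. If a fraction k of the week-12 effect is kept at week 24, the 2-df non-centrality is 7.85 × (1 − k + k²)/0.75.

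| k | Non-centrality | Power, 2 df |
|---|---|---|
| 0 or 1 | 10.47 | 0.83 |
| 0.25 or 0.75 | 8.50 | 0.75 |
| 0.5 | 7.85 | 0.71 |

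**4. Disagreement between the tests.** With 41 per arm and a 0.6 SD effect at week 12, the week-12 t-test has power of about 0.76. The interaction has 0.80, 0.67 and 0.80 for week-24 effects of 0, 0.3 and 0.6 SD. The two verdicts differ in about 12 to 13% of trials.

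**5. Change score against baseline adjustment.** Relative to the variance of a single measurement, a change score has variance 2(1 − r) and a baseline-adjusted value 1 − r². With 20% dropout, 41 × 0.80 = 32.8, so 33 per arm. Power for 0.6 SD:

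| Correlation with baseline | Change-score t-test | Baseline-adjusted |
|---|---|---|
| 0.5 | 0.67 (variance 1.00) | 0.79 (variance 0.75) |
| 0.05 (printed) | 0.41 (variance 1.90) | 0.67 (variance 0.9975) |

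**The case against.** The strongest reply rests on the verbs. The primary outcome is to be reported as t-tests, while the interaction is to test the aims formally. That can be read as descriptive reporting plus one formal test, in which case the error rate is 5%. With complete data, a change-score t-test also estimates the same difference in change as one component of the interaction, so the two are closely related. Both points have force, and inflation can therefore be stated only conditionally. They do not remove the gap: the article ties the t-tests, not the interaction, to the primary outcome, names no deciding time point, and the interaction over three times is not a single contrast.

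Three stronger readings are tempting but unsupported.

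- A reader might infer that the t-tests contradict intent-to-treat. A t-test by allocated group is compatible with that principle, and no sentence excludes dropouts. Missing-data rules may sit in a fuller document. The wear-time rule concerns the step data themselves and would bear on both analyses. What stands is narrower: unless missing values are imputed, the t-test needs both measurements while the mixed model uses available data, so the two may rest on different participants.
- A reader might infer that the omnibus test is generally weaker. It is weaker when about half the week-12 effect is kept, and stronger when all or none is kept.
- A reader might infer that the type I error is in fact about 10%. The article nowhere says that success may be claimed on any positive test.

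A full analysis plan may name the deciding test. The article, however, does not merely leave the choice open; it states two analyses.

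**Conclusion.** The point holds as a defect in how the primary analysis is fixed. Two analyses bear on steps/day, the change interval and primary time point are not stated, and neither analysis is the baseline-adjusted comparison assumed in the sample size.

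The effect on error is conditional and moderate: 5% if one test decides, about 7.5 to 10% if any positive test may be claimed. The effect on power depends on the scenario. The interaction has about 0.71 to 0.83 where a 1-df week-12 test has 0.80. The change-score t-test loses about 0.12 in power against a baseline-adjusted comparison at correlation 0.5, and about 0.26 at the printed 0.05. The power figures rest on the assumed 0.6 SD effect, 33 completers per arm and equal correlation between visits; the article gives no SD or step difference against which to check them.

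**What to change.** Name one primary test: the between-group difference in steps/day at end-program (week 12/13), as a 1-df baseline-adjusted contrast from the mixed model, including all randomised participants with available data, at two-sided 5%. Specify how baseline enters (as a covariate, or with a common baseline mean for both arms), since a plain time-by-group model with free baseline means does not give this adjustment. Label the 24-week contrast, the overall interaction and any change-score t-test as secondary or supportive.

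The cost is a few sentences of analysis wording, best settled before outcome data are seen by arm. Baseline steps are already collected. The one small downside is that the 3-month follow-up result becomes explicitly secondary.
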